## Abstract

**Background:**

Certain subtypes of young onset dementia (YOD), such as the behavioural variant of FTD or the behavioural variant of AD (bvYOD), present with changes in social behaviour instead of memory impairments. These symptoms are often under-recognized, delaying the diagnosis and contributing to psychosocial problems. Impairments in social cognition (SC), an important affected domain in bvYOD, underlie these social behavioural changes. Especially emotional blunting and a lack of empathy in patients with bvYOD might be related to problematic social behaviour, such as risk-taking behaviour, which may potentially harm others. However, despite the importance of SC impairments in the diagnosis of YOD and the impact of SC impairments on social behaviour, there is a lack of valid and well normed measures for certain aspects of SC, such as emotion experience and empathy.

**Methods:**

The YOD-RiSoCo study is an observational prospective cohort study, consisting of two separate, but related, studies. Study 1 includes 64 patients with bvYOD and 64 healthy controls to assess the sensitivity and validity of newly developed SC instruments for measuring emotion experience and empathy, by comparing their average group performance. Furthermore, validity of the new instruments will be assessed by analysing the associations of performances on these new tests with those on more traditional SC and other neurocognitive tests. Study 2 focuses on assessing to which extent SC measures relate to risk-taking behaviour. This study includes 20 patients with bvYOD and 20 healthy controls from Study 1, in addition to 20 patients with non-bvYOD (e.g. Alzheimer’s dementia or vascular dementia) and 20 patients with serious brain injury affecting frontal networks. A specific question is whether the relationship between SC and risk-taking behaviour is generic (for all groups with SC impairments), or specific (not in dementia without SC impairments).

**Discussion:**

Results of the YOD-RiSoCo study will yield new, sensitive neuropsychological tests for aspect of social cognition, which may contribute to a more timely diagnosis of YOD, allowing earlier provision of appropriate counselling and care for patients and their close others. Furthermore, the study will contribute to a better identification of those social behavioural symptoms that negatively affect functioning and social relations.

**Trial registration:**

The trial is registered at www.clinicaltrials.gov with identifier NCT06286293

## Background

Young-onset Dementia (YOD) refers to dementia with the onset before the age of 65 [1,2]. The global age-standardized prevalence of YOD is approximately 119 per 100.000 population [2]. Alzheimer’s disease (AD), vascular dementia (VD), and frontotemporal dementia (FTD) are the dominant causes of YOD, including various different subtypes as well [2,3]. Characteristic of YOD, other than in later-onset dementia, is that memory impairments are not predominant, and may not be present until later in the disease process [4]. In some variants of YOD, such as the behavioural variant of frontotemporal dementia or the behavioural variant of Alzheimer’s dementia, YOD can present in its early stages with social behavioural changes. These social behavioural changes can include behaviours that have a negative impact on other people, or can even endanger them, such as disinhibition, aggression and risk-taking behaviour. Symptoms in the early disease stages of YOD, especially changes in social behaviour, are often under-recognized, which delays the diagnosis and often contributes to psychosocial problems [5–7].

Related to these behavioural changes is social cognition (SC), an important affected domain in the behavioural variants of YOD (bvYOD), which underlies the abilities to exhibit appropriate social behaviour. Social cognition concerns the ability to perceive socially relevant information, understand the thoughts, feelings and intentions of others and respond adequately [8]. Important aspects of SC are the recognition of facial expressions of emotions, perspective taking (also referred to as mentalizing or Theory of Mind [ToM]), and empathy. ToM can be divided into cognitive ToM, concerning the ability to assess another’s thoughts and knowledge, and affective ToM, concerning the ability to assess another’s feelings and emotions through cognitive processes [9]. Empathy on the other hand, is a more emotional process of sharing in another’s affective state and feeling with another’s emotions [9].

In patients with bvYOD, impairments can occur in all these aspects of SC, and especially emotional blunting and a lack of empathy are often reported by close others [10]. This lack of emotion experience and empathy might be related to problematic behaviour, such as risk-taking behaviour, as patients do not experience the signalling function of emotions, such as fear, to warn them for possible risks [11,12]. Furthermore they might also be unable to sufficiently experience the emotional impact of their actions on other people [11,12]. There is already some evidence of a relationship between SC aspects, including empathy, and problematic social behaviour, such as risk-taking behaviour [13–15]. However, studies into the relationship between empathy and risk-taking behaviour assess empathy with subjective questionnaires, or indirect measures, such as (functional) imaging data, for empathy, instead of performance-based measures.

Despite the importance of SC in the diagnosis of YOD and the impact of SC impairments on social behaviour, such as risk-taking behaviour, there is a lack of sensitive and valid neuropsychological tests for measuring SC aspects. To date, only tests for emotion recognition, and some ToM tests are validated and widely used. No valid performance-based instruments exist to measure the ability to experience emotions and to feel with another (empathy).

In conclusion, we state that 1) people with bvYOD often present with problems in social cognition and social behaviour, 2) impairments in different aspects of social cognition (emotion recognition, ToM, emotion experience and empathy) are related to problematic social behaviour, such as risk-taking behaviour, and 3) to date there is a lack of valid and reliable performance-based measures for these aspects of social cognition, in particular empathy and emotion experience, that are also predictive of such negative social behaviours. Therefore, the main aims of the YOD-RiSoCo study are the following:

1)Assess sensitivity of new performance-based SC measures (including emotion experience and empathy) ◊ Study 12)Assess construct validity of the new performance based SC measures ◊ Study 13)Assess the relationship between social cognition and unsafe risk-taking behaviour (measuring ecological validity of the new SC tests), and investigate if this relationship is generic (by including patients with brain injury affecting frontal networks) or specific (by including patients with non-bvYOD variants, for whom no SC impairments or risk-taking behaviour are expected) ◊ Study 2

As a result of this study, we hope to introduce new, sensitive neuropsychological instruments which may aid in a more timely diagnosis of bvYOD and a better identification of social behavioural symptoms in general.

## Methods and materials

### Study design study 1

Study 1 of the YOD-RiSoCo study is an observational prospective cohort study, that aims to include 64 patients with bvYOD and 64 healthy controls. Controls will be matched to patients on a group level, so that sex, age, and educational level distributions do not significantly differ between groups. The recruitment of controls will be adapted to match the included patients.

### Study design study 2

Study 2 of the YOD-RiSoCo study is an observational study that aims to include 20 patients with bvYOD, 20 healthy controls, 20 non-bvYOD patients and 20 patients with brain injury affecting frontal processes. The bvYOD and healthy control patients will be included from Study 1 (Fig 1).

**Fig 1 pone.0324517.g001:**
[figure not shown]
Flow-chart study design.

### Study population

#### Inclusion and exclusion criteria Study 1.

All participants must have sufficient command of the Dutch language and must be between 18 years and 70 years of age. Patients in the bvYOD group must have a probable diagnosis of young-onset (start of symptoms before 65 years old) bvFTD according to the current criteria [16], or bvAD according to current criteria [17,18], or another YOD subtype in which social behavioural changes are prominent, confirmed after interdisciplinary consensus meeting in which interviews, neuropsychological examination, neurological and psychiatric assessments, neuro-imaging, blood samples, and in some cases FDG/PIB-PET-scans, CSF biomarkers, or genetic counselling were discussed. Furthermore, patients must still have the capacity to consent to participate in the study, and be able to undergo a neuropsychological assessment. Capacity to consent was determined by a Clinical Neuropsychologist, based on the neuropsychological assessment. This consent procedure is approved by the ethics committee of the University Medical Center Groningen.

Exclusion criteria for bvYOD are presence of (premorbid) severe neurological or psychiatric pathology (e.g., severe depression, schizophrenia, substance abuse) non-related to dementia. For healthy controls the exclusion criteria are presence of serious psychiatric disorders or a history of neurological disorders, which may interfere with cognitive functioning (e.g., recent concussion, previous subarachnoid or intracerebral haemorrhage, intracranial tumours, epilepsy or ischemic stroke).

#### Inclusion and exclusion criteria Study 2.

All participants must have sufficient command of the Dutch language, be between 18 years and 70 years of age, and have any driving experience in the past five years. Non-bvYOD subjects are required to have a probable diagnosis of young-onset dementia (start of symptoms before 65 years old), other than a behavioural YOD subtype (such as bvFTD, or bvAD), for example amnestic variant AD (according to McKhann criteria[18]), confirmed after interdisciplinary consensus meeting. Inclusion criteria for patients with brain injury are a brain injury, such as moderate to severe traumatic brain injury, stroke, or a brain tumour, impacting frontal processes. Furthermore, all patients must still have the capacity to consent to participate in the study and be able to undergo a neuropsychological assessment. Capacity to consent was determined by a Clinical Neuropsychologist, based on the neuropsychological assessment. This consent procedure is approved by the ethics committee of the University Medical Center Groningen

Exclusion criteria for subjects with non-bvYOD or brain injury are presence of (premorbid) severe neurological or psychiatric pathology non-related to dementia or brain injury.

The in- and exclusion criteria described for bvYOD and healthy subjects in Study 1 also apply for bvYOD and healthy subjects participating in Study 2.

#### Recruitment.

Patients with YOD will be recruited from the memory clinic (Alzheimer’s centre) of the University Medical Center Groningen (UMCG), memory clinics of local regional hospitals, and other academic memory clinics that are part of YOD-INCLUDED. Patients with brain injury impacting frontal processes will be recruited from the department of Neurology, subdepartment Neuropsychology, of the UMCG. Healthy controls will be recruited through convenience sampling by distributing flyers with information about the study and a call to participate. In addition, patients with YOD and healthy close others can also be included through the JMD (‘*Jonge mensen met dementie en hun naasten’*, which is Dutch for ‘Young people with dementia and their close others’) study of YOD-INCLUDED. YOD-INCLUDED is a Dutch national consortium, which the YOD-RiSoCo study is part of, aimed at improving diagnoses and care for patients with YOD. The JMD study is a national cohort study, for which patients with YOD and their close others can sign themselves up. Patients with YOD and healthy close others, who take part in the JMD study, will be invited to participate by the JMD research assistant through e-mail. They can also apply themselves for the module “YOD RiSoCo” in their personal dashboard of the JMD study, at www.yod-incuded.nl/jongemensenmetdementie.

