#### Study 1 New SC instruments.

Independent samples t-tests (or a non-parametric alternative, such as chi-square or Mann-Whitney U tests) will be performed to assess if the newly developed tasks can differentiate patients with bvYOD from healthy controls, based on social cognition, on a group level.

Construct validity of the newly developed measures will be assessed with parametric (such as Pearson’s correlation), or if more appropriate, non-parametric (such as Spearman’s) correlation analyses between the newly developed SC instruments, and existing SC instruments and other cognitive tests, respectively. It is expected that the new SC tests are significantly correlated to existing SC tests, indicating that the tests fall within the SC domain (convergent validity). However, no high correlation is expected, as the new tests measure different aspects of SC. No significant correlations are expected between the new SC tests and other cognitive measures (such as memory and attention), indicating that the tests measure SC specifically and no other cognitive domains, such as memory and attention (divergent validity).

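### Recruitment allows a patient and that patient's own close other on opposite sides of the main Study 1 contrast, but only independent-samples tests are named

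*Protocol article*

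**What the plan says.** All references are to the protocol article.

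- **Source of controls (Recruitment).** The first source named is flyers: "Healthy controls will be recruited through convenience sampling by distributing flyers with information about the study and a call to participate". A further route follows: "patients with YOD and healthy close others can also be included through the JMD" study. That cohort is described thus: "The JMD study is a national cohort study, for which patients with YOD and their close others can sign themselves up". Both kinds of member are then approached: "Patients with YOD and healthy close others, who take part in the JMD study, will be invited to participate by the JMD research assistant". They may also apply on their own initiative.
- **Eligibility (Inclusion and exclusion criteria, Study 1 and Study 2).** Neither section excludes a control who is related to, or is the close other of, an enrolled patient.
- **Design (Study design study 1).** There are 64 bvYOD patients and 64 healthy controls. Matching is not by individual pairs: "Controls will be matched to patients on a group level, so that sex, age, and educational level distributions do not significantly differ between groups".
- **Test (Statistical analysis, Study 1).** "Independent samples t-tests (or a non-parametric alternative, such as chi-square or Mann-Whitney U tests) will be performed" to compare the two groups on the new instruments. The Sample size section makes this difference the main outcome.
- **General provisions (Statistical analysis).** Assumptions are to be checked, with a non-parametric fallback for data that are not normal, and potential confounders are to enter as covariates. Pairs and clustering are not mentioned.

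**The concern.** A two-sample t-test, a Mann-Whitney test and a chi-square test all take the two groups to be independent. A patient and that patient's own close other may resemble each other in background, so their scores may be correlated. The recruitment plan permits this dependence and the named tests ignore it. A check of normality would not reveal it, and matching on group distributions does not remove it.

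At stake is the validity of the SE, and so of the confidence interval and the actual type I error, for the study's main contrast. The estimated difference in means is not biased by the pairing. There is also a matter of timing. The analysis model can be settled later, but who belongs to whom is easiest to record at enrolment, and the Results section puts recruitment between January 2025 and the end of 2026.

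**Working it through.** **Inputs from the protocol.** 64 per group, effect size 0.5 (read as a standardised mean difference, SD = 1), two-sided alpha 0.05, power 80%.

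**The plan's own figure.** The normal approximation gives n = 2 × (1.960 + 0.842)² / 0.5² = 62.8, rounded up to 63 per group. The noncentral t calculation gives 63.77, rounded up to 64, with power 0.801 at 64. The stated sample size reproduces.

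**Inputs the protocol does not give (assumed, shown as a range).** f is the share of each group that belongs to a patient/close-other pair. rho is the within-pair correlation of scores. If covariates are fitted, rho is what remains after adjustment.

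**Variance of the group difference.** With f × n pairs across the groups:

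Var = SD²/n + SD²/n - 2 × (f × n) × rho × SD²/n² = (2 × SD²/n) × (1 - f × rho).

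The independent-samples test uses 2 × SD²/n. Its SE is therefore the true SE multiplied by 1/sqrt(1 - f × rho).

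**Consequences (normal approximation).** SE_ind = sqrt(2/64) = 0.1768 and SE_true = 0.1768 × sqrt(1 - f × rho).

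- Actual alpha = 2 × [1 - Φ(1.960 / sqrt(1 - f × rho))]
- Power of the independent test = 1 - Φ((1.960 × SE_ind - 0.5) / SE_true)
- Power with the correct SE = 1 - Φ(1.960 - 0.5 / SE_true)

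Example for f = 0.5, rho = 0.3: sqrt(1 - 0.15) = 0.922, so SE_true = 0.1630. The SE is overstated by 1/0.922 - 1 = 8.5%. Power of the independent test is 1 - Φ((0.3465 - 0.5)/0.1630) = 0.827. With the correct SE it is 1 - Φ(1.960 - 3.068) = 0.866.

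| f | rho | SE error | Actual alpha | Power, independent test | Power, correct SE |
|---|---|---|---|---|---|
| 0 | any | 0% | 0.050 | 0.807 | 0.807 |
| 0.10 | 0.2 | +1.0% | 0.048 | 0.810 | 0.815 |
| 0.25 | 0.2 | +2.6% | 0.044 | 0.814 | 0.827 |
| 0.50 | 0.3 | +8.5% | 0.034 | 0.827 | 0.866 |
| 0.50 | -0.2 | -4.7% | 0.062 | 0.796 | 0.769 |

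**Check by simulation** (40,000 runs, 64 per group, ordinary two-sample t-test). The rejection rate under no difference was 0.046 for f = 0.25, rho = 0.2; 0.033 for f = 0.5, rho = 0.3; and 0.062 for f = 0.5, rho = -0.2. At an effect of 0.5 the rates were 0.806, 0.823 and 0.791. These agree closely with the formulas.

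**The case against.** The strongest case against has four parts.

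1. **Pairs are permitted, not planned.** Flyers come first for controls and memory clinics first for patients; the cohort is an added route. It covers young-onset dementia in general, so a close other whose patient is not bvYOD, or is not enrolled, forms no pair across the Study 1 contrast. This stands. A reader might infer that the SE of the main contrast is wrong as a matter of fact. The documents do not support that: with no pairs, or no correlation, it is exactly right.
2. **The size and sign of rho are unknown.** One might picture spouses who share a household, age and schooling, but the text says only close others and does not define the relationship. This also stands, and it is why the table includes a negative value.
3. **Covariates and assumption checks are already promised.** Adjustment for age, sex and education would remove the part of rho that they cause. It would not remove the rest, and the only remedy the plan attaches to its assumption checks concerns normality.
4. **With positive rho the test is merely conservative.** That is true, and power does not fall below plan. But the sign cannot be known without recorded pairs, and an interval of the wrong width is still a defect.

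It can also be said that clustering belongs in an analysis plan, which is not shown. The point does not rest on that silence. It rests on two things the article does state: a recruitment route that allows linked participants, and tests that assume there are none.

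**Conclusion.** The point holds conditionally and is minor. The recruitment route allows dependence between the compared groups, and the named tests make no allowance for it. If pairs enrol and their scores correlate positively, with f of 0.1 to 0.5 and rho of 0.2 to 0.3, the SE is about 1% to 9% too wide and the type I error about 0.048 to 0.034. The power lost relative to a correct SE is at most about 4 points (0.866 - 0.827). If rho is negative, the error reverses: at f = 0.5 and rho = -0.2 the SE is about 5% too narrow and the type I error about 0.06. Both f and rho are assumptions.

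Two further inferences should be resisted. The sample size of 64 per group is not undermined, since with positive rho power stays above the planned 80%. Nor is an excess of false positives the expected result, because it would need a negative within-pair correlation, which nothing in the documents suggests.

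**What to change.** - **At enrolment.** Add a field to the eCRF that links each close-other control to the enrolled patient, if there is one. Key it to the patient, so that two close others of one patient fall in the same cluster.
- **Main analysis.** Keep the group comparison and the planned covariates, but use an SE clustered on the pair, with every unpaired participant as a separate cluster. With f = 0.25 there would be 16 pairs and 96 singletons, so 112 clusters. A mixed model is an alternative if its within-pair covariance may be negative; a simple random intercept does not allow that. A paired t-test does not fit a partly paired sample. Where a score is unsuited to a comparison of means, a bootstrap that resamples whole pairs follows the same logic.
- **Sensitivity analysis.** Repeat the comparison once without the close-other controls whose patient is enrolled.

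Barring both members of a pair from enrolling would also settle the matter, but it gives up eligible participants.

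The cost is one extra field and slightly more analysis work, with no additional participants. If few pairs enrol, the gain is small.

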### Study procedures

Patients are provided with written information about the study by their clinician (e.g., geriatrician, neurologist, or (clinical) neuropsychologist), after diagnosis. This includes information about the study, participation, and an informed consent form, to read through at home. Two weeks after receiving the information and informed consent, patients are called by the researcher to make sure patients are fully informed and to create the possibility to ask questions regarding the study. If patients do not wish to be called, they can inform the investigator. When written informed consent is received, participants will be contacted by the researcher to schedule an appointment for the assessment. Data from tests that are administered to patients in a prior neuropsychological assessment will be obtained with the patient’s permission, if the neuropsychological assessment took place in the last 6 months (for patients with YOD) or two years (for patients with brain injury). These tests will then be omitted in the study assessment.

#### Study 1: Assessment procedure.

The assessment consists of several neuropsychological tests and questionnaires, and a short anamnesis concerning demographic characteristics (Fig 1). Some tasks are pencil-and-paper tasks, other tasks are computerized. The total duration of the assessment is 2.5 to 3 hours, including a short break.

#### Study 2: Assessment procedure.

Study 2 consists of the same assessments as study one and includes three additional neuropsychological tasks and a driving simulator task (Fig 1). The total duration of Study 2 is approximately 4.5 hours, including a lunch break.

### Data collection Instruments

#### General information.

Demographical characteristics (age, sex, and educational level) and data with regard to the diagnosis (e.g., imaging, biomarker and genetic data) will be collected to describe the included patient groups and to account for possible confounding factors.

